### Data collection

#### Data collection methods and participant retention

The primary and secondary outcome data collected for this trial is data that is already being collected as part of the standard follow-up of clubfoot patients at the Pehla Qadam clubfoot clinic. Therefore, no additional interventions will be done to increase the retention of participants beyond the counseling already offered to parents/caregivers of a child with clubfoot.

Assessors will not require any additional training beyond the training they receive to assess children in the clinic. The program coordinator will extract the necessary data for the trial from the Pehla Qadam logbooks after each clinic day and record it in the data tracking sheet.

### Data analysis and statistical methods

#### Interim analysis

During the RCT, one safety check will be done when 50% of the required feet are enrolled and the 3-month follow-up has been completed for these feet. The data sheet will be shared by the program coordinator with the Indus Hospital Research Center (IHRC) who will perform the interim analysis. The IHRC is not involved in the direct implementation of the trial nor in performing tenotomies or supervising residents in the clinical setting. The results of the interim statistical analysis will not be shared with the research team, if no statistical difference (non-inferiority) is observed between both groups or if the blade tenotomy shows to be statistically significantly inferior to the needle tenotomy. The trial will continue as planned in both of those cases. In case that a statistically significant difference was to be observed, and the needle tenotomy is inferior to the blade tenotomy, the trial will be ended based on the assumption that non-inferiority cannot be proven and patients should not be needlessly exposed to an inferior tenotomy technique.

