#### Sample size and power calculation

Sample sizes are calculated using the WHO sample size determination software [22].

Sample size calculation for primary outcome:Alpha = 5%Power 95%Non-inferiority margin: 4Standard deviation: 9.02

Required sample size = 222 feet (111 in each arm).

Drop-out from clubfoot programs is a common event in LMICs, especially throughout the bracing phase. In literature, drop-out rates of up to 30% have been reported over the total period of bracing which is about 3 years on average [17, 18, 23]. Internal data from the Pehla Qadam clubfoot program shows similar outcome with about 30% drop-out over the entire course of the treatment. We therefore expect during the first year of follow-up to lose about 10% of our patients. We will therefore increase the sample size by 10% to adjust for the expected drop-out.

A total sample size of 244 feet (122 per arm) will be recruited for this trial.

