#### Outcomes

Group A will be compared to group B for the primary and secondary analyses. A multi-level mixed-effects regression model will be used to assess the outcomes. An overview of the different variables to be assessed can be found in Table 1. A linear regression model will be used for the continuous variables and a logistic regression model for the binary variables. If a child received a tenotomy on both feet, these two feet will be clustered, and the analysis must make an adjustment for the lack of independence between measures on these two feet. A mixed-effects model allows for the inclusion of a random subject effect to the regression model, accounting for correlation between pairs of feet on the same child and also assessing the treatment effect from both between-subject differences and within-subject differences. Stata Version 17 (StataCorp, TX, USA) will be used for the analysis. A *p*-value < 0.05 will be considered significant. We will use the one-tailed *p*-value for all our analyses.

**Table 1 Tab1:** Clinical outcomes and proposed statistical analysis

Variable/outcome	Hypothesis	Outcome measure	Method of analysis

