**Secondary outcomes**			
Pirani score at 3 weeks post-tenotomy	Equal score	Pirani score with 0.5-point increments	Multi-level mixed effects linear regression
Pirani score at 3 months post-tenotomy	Equal score	Pirani score with 0.5-point increments	Multi-level mixed effects linear regression
Minor complications at 3 weeks post-tenotomy	Equal count	Number of minor complications	Multi-level mixed effects logistic regression
Minor complications at 3 months post-tenotomy	Equal count	Number of minor complications	Multi-level mixed effects logistic regression
Major complications at 3 weeks post-tenotomy	Equal count	Number of major complications	Multi-level mixed effects logistic regression
Major complications at 3 months post-tenotomy	Equal count	Number of major complications	Multi-level mixed effects logistic regression
*Complication subgroup analysis*	*Equal count*	*Number of specific type of complications*	Multi-level mixed effects logistic regression

Non-inferiority will be established if the confidence interval for the needle group does not cross the non-inferiority margin. In practice, this means a confidence interval including only values < 4. If the confidence interval includes the value 4, the trial will be determined inconclusive. If the confidence interval only values > 4, the needle tenotomy technique will be considered inferior to the blade technique.

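### The interim stopping rule is worded without the 4° margin and conflicts with the final decision rule; on its plain reading it can end the trial while non-inferiority is still attainable

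*Protocol article*

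**What the plan says.** The Interim analysis section plans one look, when half of the required feet have been enrolled and have completed 3-month follow-up. It distinguishes three cases:

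- The trial continues "if no statistical difference (non-inferiority) is observed between both groups".
- It also continues if the blade is statistically significantly inferior.
- It ends if there is a statistically significant difference with the needle worse. The reason given is "based on the assumption that non-inferiority cannot be proven and patients should not be needlessly exposed to an inferior tenotomy technique".

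The section names neither an outcome nor a margin.

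The Outcomes section under Data analysis sets significance at p < 0.05 and adds: "We will use the one-tailed *p*-value for all our analyses".

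The decision rule below Table 1 works on a different scale. Non-inferiority needs a confidence interval wholly below 4°. An interval that includes 4° is inconclusive. Only when the interval lies wholly above 4° does the protocol say that "the needle tenotomy technique will be considered inferior to the blade technique".

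The sample size section gives the design inputs as "Alpha = 5%Power 95%Non-inferiority margin: 4Standard deviation: 9.02", with 222 feet required and 244 recruited. It makes no allowance for the interim stop.

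**The concern.** The needle can be called inferior under two standards that lie far apart. The interim text describes a test of difference and labels non-significance as non-inferiority. The final rule judges an interval against a margin. A deficit that differs significantly from zero at half the sample need not exceed 4°, and it does not rule out a final interval below 4°. The trial could therefore end, with the needle described as inferior, on data that its own final rule would call inconclusive. The reason given for ending it would not be correct, and the stated 95% power leaves out the chance of such a stop. The hospital research center runs this look and there is no data monitoring committee, so the written rule has to be unambiguous.

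**Working it through.** **Inputs.** From Sample size and power calculation: SD 9.02°, margin 4°, alpha 5%, power 95%, 222 feet before and 244 after the drop-out allowance. From Outcomes: one-tailed tests at 0.05. From Interim analysis: a look at half the feet.

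**Assumptions.** The outcome tested is 3-month dorsiflexion. The null value is zero. Feet are independent, as in the plan's own calculation. Intervals are the estimate ± 1.645 SE, which matches one-sided 0.05.

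**The plan's own figure.** Per arm, n = 2 × [9.02 × (1.645 + 1.645) / 4]² = 110.06, rounded up to 111, or 222 feet. This reproduces. One-sided 0.025 would give 266, so the design is at one-sided 0.05.

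**Where the interim rule fires.** SE = 9.02 × √(2/n), with n per arm at the look. The cut-off against zero is 1.645 × SE, and against the margin it is 4 + 1.645 × SE.

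| Feet at look | SE | Stop against 0 | Interval at that stop | Stop against 4° |
|---|---|---|---|---|
| 111 (of 222) | 1.712 | 2.82° | 0 to 5.63° | 6.82° |
| 122 (of 244) | 1.633 | 2.69° | 0 to 5.37° | 6.69° |

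Both intervals at the zero-based stop contain 4°, which is the inconclusive case under the rule below Table 1.

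**Is non-inferiority out of reach at that stop?** With 222 feet the final SE is 9.02 × √(2/111) = 1.211, so success needs a final estimate below 4 − 1.645 × 1.211 = 2.01°. A trial at exactly 2.82° needs a second-half difference below 2 × 2.01 − 2.82 = 1.20°. The chance of that is Φ((1.20 − true difference) / 1.712):

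- true difference 0: 76%
- true difference 1°: 55%
- observed trend continuing: 17%

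With 244 feet the figures are 82%, 62% and 24%.

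**Overall effect of the stop.** Interim and final estimates are bivariate normal with correlation √0.5. The cells give 222 feet / 244 feet.

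| True deficit | Trials stopped | Success without the look | Success with the stop | Stopped trials that would have succeeded |
|---|---|---|---|---|
| 0° | 5.0% / 5.0% | 95.1% / 96.6% | 92.1% / 93.1% | 61% / 69% |
| 1° | 14.4% / 15.1% | 79.8% / 83.0% | 74.5% / 76.5% | 36% / 43% |
| 2° | 31.7% / 33.7% | 50.3% / 53.5% | 45.2% / 46.8% | 16% / 20% |

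At a true deficit of 2° the trials lost are 50.3 − 45.2 = 5.1% or 53.5 − 46.8 = 6.7% of all trials. A stop against the margin at one-sided 0.05 fires in under 0.1% of trials at a true deficit of 0° or 1°, and leaves power unchanged there.

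**Sensitivity to the interim level.** If the look used one-sided 0.025 and the final analysis stayed at 0.05, the zero-based stop would be at 3.36° (111 feet) or 3.20° (122 feet), still below 4°. The power loss at zero difference would be 1.3 to 1.5 points.

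**The case against.** The interim section never writes that the null value is zero. Its stop has two parts, a significant difference and an inferior needle, and the only definition of an inferior needle is the one below Table 1. If that definition is imported, the rule is margin-based and the zero-based figures fall away. A reader might therefore go too far in stating as fact that the rule tests against zero. That is the plain reading, because the three cases are no difference, blade significantly worse and needle significantly worse, with the first labelled non-inferiority. It remains an inference, as does the choice of 3-month dorsiflexion as the outcome. What holds on either reading is that the text permits two cut-offs 4° apart.

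A reader might also infer that a third of trials are wrongly lost at a true deficit of 2°. The figures do not support this. About a third stop, but only 16–20% of those would have succeeded.

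Nor is non-inferiority likely once the rule has fired: 17–24% at the cut-off if the trend continues, and less for larger deficits. An early stop that protects children at a cost of about 3 points of power is a defensible choice. It has to be described as that choice, not justified by a claim that non-inferiority can no longer be shown.

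Finally, the interim criterion should not be read as the trial's only safeguard. Harms and adverse events sets out separate monitoring of tenotomy-related events and reporting of serious ones to the IRB.

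**Conclusion.** The point holds as a conflict between two stated rules, with a stopping rationale that is incorrect on the plain reading and a power figure that omits the stop. Under the listed assumptions, the stop comes at an observed deficit of 2.7°–2.8°, inside the margin, on an interval that the final rule calls inconclusive. The cost in power at zero difference is 3.0 points (222 feet) or about 3.4 points (244 feet). The stop can only end the trial without a claim, so it does not raise the risk of falsely declaring non-inferiority. The more serious consequence is interpretive: a stopped trial could be reported as having shown inferiority when the protocol's own standard would not support that.

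**What to change.** Reconcile the Interim analysis section with the rule below Table 1. State the outcome tested, the test level, and whether the criterion is relative to 0 or to the 4° margin. Replace the continuation condition "if no statistical difference (non-inferiority) is observed between both groups" with a statement that the stopping criterion was not met.

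Then follow through on whichever criterion the sponsor chooses:

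- **Test against zero kept.** Delete the rationale that non-inferiority cannot be proven. State that a stopped trial is not reported as having shown inferiority under the final rule. Restate power as about 92% (222 feet) or 93% (244 feet).
- **Margin-based criterion.** State that at one-sided 0.05 it needs an observed deficit of about 6.7°–6.8° and will rarely fire: in 5% of trials even at a true deficit of 4°, and less often at a stricter level. Power at small true deficits is then unchanged, but the early stop gives little protection.

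The cost is a few sentences, plus either a slightly lower stated power or a stop that seldom acts. The wording should be settled before the look. If the look has already taken place, the criterion that was applied should be reported.

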#### Outcomes

Group A will be compared to group B for the primary and secondary analyses. A multi-level mixed-effects regression model will be used to assess the outcomes. An overview of the different variables to be assessed can be found in Table 1. A linear regression model will be used for the continuous variables and a logistic regression model for the binary variables. If a child received a tenotomy on both feet, these two feet will be clustered, and the analysis must make an adjustment for the lack of independence between measures on these two feet. A mixed-effects model allows for the inclusion of a random subject effect to the regression model, accounting for correlation between pairs of feet on the same child and also assessing the treatment effect from both between-subject differences and within-subject differences. Stata Version 17 (StataCorp, TX, USA) will be used for the analysis. A *p*-value < 0.05 will be considered significant. We will use the one-tailed *p*-value for all our analyses.

**Table 1 Tab1:** Clinical outcomes and proposed statistical analysis

Variable/outcome	Hypothesis	Outcome measure	Method of analysis

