### Outcomes

Patients will be followed as per the standard follow-up schedule at the Pehla Qadam clubfoot clinic. Patients will be evaluated at 3 weeks and at 3 months post-tenotomy during regular follow-up consultations. The dorsiflexion range at 3 months post-tenotomy is considered the primary outcome. These measurement points were chosen as they coincide with the standard follow-up appointments established at the Pehla Qadam clubfoot clinic. Given that long-term follow-up is challenging in low-resource settings, the primary outcome measure was the first follow-up visit after cast removal, i.e., 3 months post-tenotomy to minimize drop-out from the trial.

The primary outcome measure is as follows: range of dorsiflexion will be registered at both follow-up visits.

The secondary outcome measures are as follows: complications including neurovascular damage in the heel region, skin, and wound problems or infections will be recorded at both follow-up visits. Neurovascular damage, an infection requiring antibiotic treatment or any other type of complication that requires the consultation of another medical specialty, will be considered a major complication. Scar hypertrophy, local edema, or erythema will be considered minor complications.

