### Intervention allocation

The Indus Hospital Research Center (IHRC) will prepare 244 randomization envelopes according to the SNOSE-protocol [25] at their office before the start of enrollment of patients in the clinic. Only the exact number of envelopes necessary to carry out this study will be prepared. The envelopes are sequentially numbered and contain group allocation information for the patient allocation. Group information will be inserted in the envelopes using permutated blocks of random sizes according to the SNOSE-protocol (sequentially numbered, opaque sealed envelopes) [25]. The application of the SNOSE-protocol makes it impossible to predict which group allocation will be in the upcoming envelope when allocating envelopes according to their sequential numbering and thus protects concealment of the group allocation. However, this technique also assures a 1:1 randomization of the participants at the end of the study.

All patients who meet the inclusion criteria and have an informed consent form signed by a parent will be randomized. Randomization of patients and group allocation will happen in the clinic before the tenotomy takes place. No stratification of patients takes place during the group allocation process. Each envelope will contain a piece of aluminum foil, a piece of carbon paper, and a paper containing group information.

The study team member takes the envelop with the next available sequence number when a new patient registers for the study. Before opening the envelope, a study team member will write the MR number, name, date, and study ID of the patient on the envelope. The carbon paper inside the envelope will transfer the patient details onto the paper inside the envelope, avoiding any possibility for fraud or accidental group misplacement.

In case of retraction of informed consent for the study or surgical procedure, the envelope will be returned to IHRC. When all available envelopes have been used, IHRC will provide a new set of randomization envelopes, equal to the number of returned envelopes. This procedure assures that 1:1 randomization is maintained throughout the study.

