**Primary outcomes**			
Dorsiflexion at 3 weeks post-tenotomy	Equal range of dorsiflexion	Degrees of dorsiflexion with 5° increments	Multi-level mixed effects linear regression
Dorsiflexion at 3 months post-tenotomy	Equal range of dorsiflexion	Degrees of dorsiflexion with 5° increments	Multi-level mixed effects linear regression

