Only de-identified data, using the trial tracking number for each foot instead of a personal identifier like the medical record number, will be shared with the research team. Age at time of tenotomy and at time of the two follow-up visits will be calculated by the program coordinator as to avoid sharing identifiable data such as a date of birth or a date of visit.

If a participant missed one of the required follow-up visits his/her parent/caregiver will be contacted to remind them of the importance of follow-up during clubfoot treatment. They will receive the standard phone call any patient in the clubfoot clinics receives when they miss an appointment. If a patient has not returned for follow-up after within 6 months of his/her last scheduled follow-up appointment, the patient’s enrolled foot/feet will be labeled as “lost to follow-up” for both the program’s purpose as well as for the trial’s purposes.

Participants’ data, including de-identified data, will not be shared with anyone outside of this trial without formal written consent of the parents/caregiver or the participant him/herself once they reach the age of 18 years.

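### The primary dorsiflexion model names no baseline covariate, leaving unused the precision that prespecified adjustment for age and pre-tenotomy dorsiflexion could give

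*Protocol article*

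**What the plan says.** All references are to the protocol article.

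- **Endpoint.** Under Outcomes: "The dorsiflexion range at 3 months post-tenotomy is considered the primary outcome". Table 1 gives the measure as "Degrees of dorsiflexion with 5° increments" and the method as multi-level mixed-effects linear regression.
- **Model.** The analysis section compares group A with group B and describes one further term: "A mixed-effects model allows for the inclusion of a random subject effect to the regression model, accounting for correlation between pairs of feet". No fixed covariate appears there or in Table 1.
- **Error rate.** The threshold is 0.05, and "We will use the one-tailed *p*-value for all our analyses".
- **Allocation.** Under Intervention allocation: "No stratification of patients takes place during the group allocation process".
- **Age.** Under Data management, access and confidentiality: "Age at time of tenotomy and at time of the two follow-up visits will be calculated by the program coordinator". Eligibility runs to 36 months.
- **Starting range.** Eligibility criteria require dorsiflexion below 15°, so each foot has to be judged before tenotomy. Measurement is otherwise described only at 3 weeks and 3 months. No section says that a pre-tenotomy value in degrees enters the trial data.
- **Sample size.** "Required sample size = 222 feet (111 in each arm"), from a margin of 4°, an SD of 9.02, alpha 5% and power 95%.

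**The concern.** The trial's conclusion depends on whether a confidence interval for the arm difference stays inside 4°; an interval that includes 4 makes the trial inconclusive. In a linear model, a baseline variable that predicts the outcome takes variance out of the error term and so shortens that interval. A random child effect does a different job: it allows for two feet of one child being alike. It does not use starting range, and it does not correct a difference in mean age between the arms among children who contribute one foot.

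Because allocation is not stratified, neither the design nor the stated model deals with a chance difference between the arms in age or starting stiffness. Such a difference can move the estimate towards or away from the margin. At stake is a somewhat higher chance of an inconclusive result from the same feet and the same visits. There is also the risk that the choice between adjusted and unadjusted results is made after the data are seen.

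**Working it through.** **Step 1: reproduce the plan's figure.** Inputs from Sample size and power calculation: margin 4, SD 9.02, alpha 5% (read as one-sided, as the analysis section states), power 95%, true difference 0, feet independent.

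n per arm = 2 × SD² × (z₀.₉₅ + z₀.₉₅)² / margin² = 2 × 81.36 × (1.645 + 1.645)² / 16 ≈ 110.1, rounded up to 111, or 222 feet. This matches exactly. One-sided 2.5% would give 133 per arm (266 feet), so the plan was sized at one-sided 5% with no covariate adjustment. The stated 10% increase also matches: 222 × 1.10 = 244.2, against 244.

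**Step 2: precision of the model as described.**

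SE = 9.02 × √(2/111) = 1.211°. 
Power = Φ(4/1.211 − 1.645) = 95.1%. 
90% interval half-width (the interval that corresponds to one-sided 5%) = 1.645 × 1.211 = 1.99°.

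**Step 3: precision with adjustment.** Let rho be the multiple correlation of the covariates with 3-month dorsiflexion within arms. The documents give no value; 0.2 to 0.5 is an assumption. Residual SD = 9.02 × √(1 − rho²), and Step 2 is repeated with that SD.

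| rho (assumed) | Residual SD | 90% half-width | Power, true difference 0 | Feet needed for 95% power | Power, needle truly 1° worse |
|---|---|---|---|---|---|
| 0 (as described) | 9.02 | 1.99° | 95.1% | 222 | 79.8% |
| 0.2 | 8.84 | 1.95° | 95.8% | 212 | 81.2% |
| 0.3 | 8.60 | 1.90° | 96.5% | 202 | 83.0% |
| 0.5 | 7.81 | 1.73° | 98.5% | 166 | 88.8% |

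The last column uses Φ(3/SE − 1.645).

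**Step 4: exposure to chance imbalance.** The variance of the unadjusted difference splits into rho² × SE², due to chance imbalance in the covariates, and (1 − rho²) × SE², the rest. The first part has a standard deviation of rho × 1.211°: 0.24° at rho 0.2, 0.36° at 0.3 and 0.61° at 0.5. The unadjusted interval already allows for this part; adjustment removes it.

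**Step 5: departures from the plan's premises.** Table 1's decision rule gives no confidence level. Under a two-sided 95% interval, power goes from 91.0% to 93.4% (rho 0.3) or 96.8% (rho 0.5). With an assumed design effect of 1.25 at one-sided 5%, it goes from 90.5% to 92.7% or 96.1%. Neither premise is the one that produces 222.

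**The case against.** **The article does not exclude covariates.** It says a mixed model allows a random subject effect; it does not say that this is the only extra term. Protocol amendments refers to a consolidated analysis plan that is not shown, and covariate lists often sit in such a document. This limits the point. It does not remove it, because the article fixes model class, random effect, software, tails and a method for each outcome, and a primary model described in that detail without baseline terms can reasonably be improved where it is stated.

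**Prognostic value is not shown.** A reader might infer that known prognostic variation is being left in the error term. The documents do not support that. The cited study under Non-inferiority margin determination links range under age 3 with range kept at age 12; it says nothing about age within 0 to 36 months predicting the 3-month result. The Discussion calls the influence of walking unknown. This objection stands: the variables are plausible predictors, no more.

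**Pre-tenotomy degrees may not be recorded.** Only a threshold is stated, and an audit of eligibility does not establish a degree value for each foot. This stands. Age is the only covariate documented as available.

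**The correlation may be low.** Baseline is cut off at 15°, may be read in 5° steps like the outcome, and may be judged by a different clinician. For a child whose two feet fall in different arms, the random child effect already takes age out of the within-child comparison. All of this favours the low end of the range.

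**There is no bias and no shortfall.** A reader might also infer that the interval is too wide for the plan. It is not: 222 feet were sized on the unadjusted SD, randomization makes the unadjusted difference unbiased, and at a 95.1% start even perfect prediction could add only 4.9 points. This stands.

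**Conclusion.** The point holds as a modest matter of efficiency. The primary model as described names no baseline covariate although one is available (age) and a second may be (pre-tenotomy dorsiflexion), with unstratified allocation.

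On the plan's own inputs the gain in power is 0.7 points at rho 0.2, 1.4 at 0.3 and 3.4 at 0.5, and the 90% half-width shortens by 0.04° to 0.27°. The gain is larger if the needle is truly slightly worse: with a 1° deficit, 3.2 points at rho 0.3 and 9.0 at rho 0.5. Gains above 5 points appear only at the high assumed correlation and under a changed premise (a true deficit, a two-sided 95% interval, or an assumed design effect), so they should not be read as the cost of the plan as written.

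Everything here rests on an assumed correlation, and the 15° ceiling may keep it low. The case for acting is that the change is nearly free and that fixing the covariates in advance removes a later choice between two analyses.

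**What to change.** Before any arm data are seen, state the primary model in the analysis section and Table 1 as:

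3-month dorsiflexion = arm + age at tenotomy + pre-tenotomy dorsiflexion of that foot, both continuous, with the random child effect.

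Compare the adjusted arm difference and its interval with the 4° margin, and report the unadjusted model as a sensitivity analysis. Include pre-tenotomy dorsiflexion only where the clinic record holds the degree value, and copy it to the trial data sheet. If degrees were not recorded, adjust for age alone and say so.

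The cost is one or two degrees of freedom, at most one extra column in the data sheet and a sentence or two of text, with no added visits, measurements or children. A rule is also needed for a foot without a baseline value, for example filling in the overall mean; otherwise the model drops that foot. The section on missing data rules out imputation, so it would need a short exception for baseline covariates.

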### Objectives and hypotheses

#### Objectives

Through this study, we aim to compare the clinical outcomes in children receiving either a blade or a needle percutaneous tenotomy.

*Main research questions*: Is there a difference in clinical outcome (dorsiflexion range) after an Achilles tendon tenotomy performed with a blade or needle at 3 months post-operatively?

*Secondary research questions*: Is there a difference in secondary clinical outcomes?

Secondary clinical outcomes include the following: minor and major complication frequency and types and Pirani score at 3 months post-operatively.

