#### Hypotheses

*Main hypothesis*: Percutaneous needle tenotomy has a non-inferior clinical outcome compared to the use of a percutaneous blade tenotomy when comparing the patient’s dorsiflexion range.

*Secondary hypothesis*: Percutaneous needle tenotomy complication frequency and Pirani score are clinically comparable in frequency of complication (minor and major) and Pirani score to the percutaneous blade tenotomy.

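### The one-tailed p-value rule covers every analysis, but Pirani score and complications are posed as non-directional questions with no stated direction or margin

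*Protocol article*

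**What the plan says.** Under Data analysis and statistical methods, Outcomes, the protocol states "Group A will be compared to group B for the primary and secondary analyses", then "A *p*-value < 0.05 will be considered significant", then "We will use the one-tailed *p*-value for all our analyses". No secondary or safety outcome is exempted.

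The secondary questions are worded without a direction:
- Objectives: "Is there a difference in secondary clinical outcomes", covering Pirani score and the frequency and types of minor and major complications.
- Hypotheses: the needle technique is expected to be "clinically comparable in frequency of complication (minor and major) and Pirani score" to the blade technique.
- Table 1: the hypothesis column gives equality for every secondary row, as a score for Pirani and as a count for complications.

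The 4° margin and the confidence-interval rule printed after Table 1 concern dorsiflexion. No section gives a margin, or names the tail to be tested, for any secondary outcome.

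**The concern.** A one-tailed p-value is not defined until a direction is named. For dorsiflexion the margin and the non-inferiority frame supply it. For Pirani score and complications nothing in the text does, so the analyst must choose the tail, and each choice has a drawback. Letting the data choose makes the procedure two-directional at twice the nominal level. Fixing the tail means an effect in the other direction cannot be declared, although the research question asks whether there is any difference.

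The Rationale bases wider use of the needle, including by non-physicians, on complications as well as dorsiflexion. A safety comparison that is ambiguous in direction, and that can do little to support comparability when it is non-significant, is a weak basis for half of that argument.

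**Working it through.** **1. Does one-sided 5% belong to the primary test?** Inputs from Sample size and power calculation: "Alpha = 5%Power 95%Non-inferiority margin: 4Standard deviation: 9.02". With a true difference of 0,

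n per arm = 2 × (z₁₋α + z₁₋β)² × SD² / margin²

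- One-sided 5%: 2 × (1.645 + 1.645)² × 9.02² / 4² = 110.1, rounded up to 111 per arm, 222 in total. This is the protocol's figure.
- One-sided 2.5%: 2 × (1.960 + 1.645)² × 9.02² / 4² = 132.2, rounded up to 133 per arm, 266 in total. This does not match.

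So the one-sided 5% rule is consistent with the primary design, and nothing here disturbs it.

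**2. The secondary outcomes, tail chosen from the data.** Rejecting when the one-tailed p in the observed direction is below 0.05 means rejecting when |Z| > 1.645. The error over both directions is 2 × (1 − Φ(1.645)) = 0.10. A two-sided 5% test uses 1.960.

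This 10% is a normal-theory value. It is reasonable for Pirani score but not reliable for rare complications. Exact enumeration with 111 independent feet per arm and the same true rate in both arms, rejecting in either direction at one-tailed p < 0.05, gives:

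| True rate in both arms | Wald logistic test (tables with a zero cell count as non-rejections) | Score-type test |
|---|---|---|
| 2% | 1.3% | 12% |
| 5% | 7.5% | 11% |
| 10% | 8.9% | 10% |

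**3. The secondary outcomes, tail fixed.** The nominal error is 5%, but the other direction is out of reach. If the tail were fixed towards fewer complications with the needle, and the true rates were 2% blade and 8% needle (the 8% is an assumption), the probability of rejection would be about 0.0001.

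**4. What non-significance would show.** The Background cites a 2% complication rate for the blade. Assume 6% with the needle, 111 independent feet per arm, and a normal approximation.

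- Pooled rate 0.04; SE under the null = √(2 × 0.04 × 0.96 / 111) = 0.02630
- SE under the alternative = √((0.02 × 0.98 + 0.06 × 0.94) / 111) = 0.02617
- One-sided power = Φ((0.04 − 1.645 × 0.02630) / 0.02617) = Φ(−0.125) = 0.45
- Two-sided power = Φ((0.04 − 1.960 × 0.02630) / 0.02617) = Φ(−0.442) = 0.33

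Fisher's exact test gives less, about 30% and 21%. Over assumed needle rates of 5% to 10%, the normal approximation gives 33% to 81% one-sided and 23% to 71% two-sided. A tripling of complications would more likely than not go undetected.

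**The case against.** The best defence is that the direction can be inferred. This is a needle-versus-blade non-inferiority trial, the Rationale places complications in the same non-inferiority frame, and the interim rule stops the trial only if the needle is worse. On that reading the tail is fixed in advance towards needle harm, the error is 5% per test, and being unable to declare the needle better costs little because no superiority claim is planned. Such a test also detects harm better than a two-sided one.

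This is a plausible reading, and it makes the 10% figure conditional. It does not remove the problem. The protocol never states that direction for the secondary outcomes, and their wording asks about difference or equality. The interim section itself envisages a result in the other direction: "if the blade tenotomy shows to be statistically significantly inferior to the needle tenotomy". Naming the direction would settle the ambiguity, but without a margin a one-tailed test of difference still could not show comparability.

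Two stronger readings are tempting and should be resisted.

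- A reader might infer that the plan treats a non-significant secondary result as proof of equality. No section says so. The equality entries in Table 1 are hypotheses, and the same wording stands on the dorsiflexion rows, where the conclusion comes from the confidence interval.
- A reader might multiply the 10% over the six named secondary rows to get 1 − 0.90⁶ = 47% for at least one false positive. That assumes independence, whereas the rows are three outcomes each measured twice on the same feet. With an assumed correlation of 0.7 to 0.9 between the two visits it is about 41% to 36% on normal theory, before the caveat on rare events. Two-sided 5% tests would already give 1 − 0.95⁶ = 26% under independence, so much of the 47% is multiplicity, not sidedness.

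**Conclusion.** The blanket one-tailed rule is right for dorsiflexion and does not fit Pirani score and complications as the protocol poses them. The fault is one over-broad sentence. It leaves the primary test, the 222 feet required and the 244 to be recruited as they are.

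For Pirani score the nominal error is 10% instead of 5% if the tail follows the data; otherwise one direction is closed off. For rare complications no single error figure can be given, because it depends on the test. There the main limitation is low power, about 45% one-sided or 33% two-sided for 2% against an assumed 6%, so a non-significant result says little about comparability. The power figures rest on the cited 2%, the assumed needle rate and independent feet. The change should be made because complications carry part of the trial's rationale.

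**What to change.** Limit the one-tailed p-value to the dorsiflexion non-inferiority comparison. For Pirani score and for minor and major complications, report the between-arm difference with a two-sided 95% confidence interval, and use two-sided p-values if any are given. Replace the equality entries for the secondary rows of Table 1 with a statement that comparability will be judged from the interval and not from a non-significant p-value.

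The cost is one sentence in the methods and one column of Table 1. The sample size and primary test are untouched. The real downside is that a two-sided p-value is less likely to flag needle harm than a one-sided test aimed at harm (45% falls to 33% in the example). Reading the upper limit of the interval offsets this, since it shows how large an excess of complications remains compatible with the data.
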